### Trial objectives

In this study, the addition of PCT to TAU will be compared to TAU alone in patients that recovered from recurrent depressive disorder after treatment with A-CT. Alongside this effectiveness study a cost-effectiveness study will be done. It is hypothesized that adding PCT to TAU is clinically superior tot TAU alone in preventing relapse and recurrence of depressive disorder.

Furthermore, the study explores potential moderators to examine what works for whom. Potential mediators will also be examined to explore the working mechanism of PCT by assessing coping, social support, dysfunctional attitudes, affiliation, daily stress and functioning, and their association to risk of relapse in depression, before, during and after treatment.

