### Outcome measures/Instruments

Every participant will be monitored over a period of 15 months. After baseline assessment, follow up assessments of patients in the TAU condition will be performed at 1, 2, 3, 6, 12 and 15 months. Patients in the experimental condition will be assessed every session and after 3, 6, 12, and 15 months. The assessments done at baseline and at 15 months consist of an interview and self-report measures. Al interviews will be performed by trained assessors. The assessors are blind to the allocation of the participants. The remaining assessments are self-report questionnaires, which are filled in by the patients and their therapists. For an overview of the assessments at baseline, post treatment and follow up see Table 1. For an overview of the assessments after each session see Table 2.

**Table 1 Tab1:** Overview of assessments

Measure	Description	T0	T1	T2	T3	T4	T5	T6^a^
Interviews								
SCID-I	DSM-IV-TR Axis I disorders	x						x
HAM-D	Depressive symptoms and severity	x						x
Self report measures								
IDS-SR	Depressive symptoms	x			x	x	x	x
IIP-C	Social and interpersonal functioning	x						
EQ-5D	Quality of life	x			x	x	x	x
TIC P	Direct/indirect costs	x			x	x	x	x
PMS	Psychological mindedness	x				x		
PDQ-4	Personality				x			
Brugha	Life events	x						x
EPCL	Everyday problems	x				x	x	
Mastery scale	Mastery	x			x	x	x	x
VAMS	Mood	x			x	x	x	x
IVM	Victimization							x
SSL-I	Social support		x	x	x	x		x
UCL	Coping		x	x	x	x		x
AAQ	Experiential acceptance and avoidance		x	x	x			
ORS	Functioning		x	x	x			
Affiliation	Affiliation		x	x	x			
PANAS-X	Emotions		x	x	x			
DAS	Dysfunctional attitudes		x	x	x		x	
BDI	Depressive symptoms		x	x	x			

^a^T0 = Baseline, T1 = 1 month, T2 = 2 months, T3 = 3 months, T4 = 6 months, T5 = 12 months, T6 = 15 months

**Table 2 Tab2:** Overview of assessments after each session

Measure	Description	S1	S2	S3	S4	S5	S6	S7	S8^a^
UCL	Coping	x		x		x		x	
SSL-I	Social support		x				x		
AAQ	Experiential acceptance and avoidance		x				x		
ORS	Functioning	x	x	x	x	x	x	x	x
SRS	Session evaluation		x		x		x		x
BDI	Depressive symptoms	x		x	x	x		x	x
WAI-SR	Therapeutic relationship		x		x		x		x
DAS-17	Dysfunctional attitudes	x	x	x	x	x	x	x	x
Affiliation	Affiliation		x		x				x
Daily h.	Daily stressors	x		x		x		x	
PANAS	Emotions	x	x	x	x	x	x	x	x

^a^S = session number

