### Other parameters

As potential moderators, mediators and mechanisms of change we will analyze; personality traits measured by the Personality Diagnostic Questionnaire (PDQ-4) [34], psychological mindedness measured by the Psychological Mindedness Scale (PMS) [35], mastery measured by the Mastery scale [36], social support measured by the Sociale Steun Lijst (SSL-I) [37], coping measured by the Utrechtse Coping Lijst (UCL) [38], experiential acceptance and avoidance measured by the Acceptance and Action Questionnaire (AAQ-II) [39], functioning measured by the Outcome Rating Scale (ORS) [40], affiliation measured by the Affiliation scale [41], emotions measured by the Positive and Negative Affect Schedule (PANAS-X) [42], dysfunctional attitudes measured by the Dysfunctional Attitude Scale (DAS) [43, 44], social en interpersonal functioning measured by the Inventory of Personal Problems (IIP-C) [45], depressive mood measured by a one item mood scale [46], session evaluation measured by the Session Rating Scale (SRS) [47], therapeutic relationship measured by the Working Alliance Inventory-Short Revised (WAI-SR) [48], mood measured by a one-item Visual Analogue Mood Scale (VAMS) [46] and Victimisation measured by the Dutch version of the Integral Safety/Security Monitor (IVM) [49].

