### Analysis

The primary outcome measure will be the time to relapse or recurrence meeting DSM-IV criteria for a major depressive episode on the Structured Clinical Interview for DSM-VI (SCID-I). Occurrence of relapse or recurrence (current or since the last assessment point) will be assessed after 15 months, by trained psychologists who are blind to the treatment condition. Cox regression analysis will be performed. Analysis will be conducted by intention to treat, including all subjects randomized in the study, and per protocol. Statistical significance will be set at p < .05. The time (in weeks) of relapse or recurrence to Major Depression, as defined above, will be the dependent variable in survival analysis. The treatment group will be used as predictor, and the stratification variable will be used as covariate. In addition, time since previous episode and time since last treatment will be included as covariates.

In addition, we use the HAM-D, to assess the severity of depression at both time points, together with the SCID-I.

Mixed-model analysis will be used for the quantitative measures. As covariates we will use the stratification variable (number of episodes). Potential moderators to be examined include gender, residual symptoms of depression, duration of remission, duration of last episode, coping, age of onset and current use of AD.

For the economic evaluation the relationship between costs and health outcomes of the two treatment conditions will be evaluated using a societal perspective. Both a cost-effectiveness analysis with depression-free survival time as effect measure and a cost-utility analysis with QALYs as effect measure will be performed.

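### Coping is a listed moderator, and mediators are promised before treatment, but coping and four of the other five named mediators have no baseline measurement in Table 1

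*Protocol article*

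**What the plan says.** The Analysis section lists seven potential moderators: "Potential moderators to be examined include gender, residual symptoms of depression, duration of remission, duration of last episode, coping, age of onset". The seventh is whether the patient takes antidepressants. Other parameters names the coping instrument: "coping measured by the Utrechtse Coping Lijst (UCL".

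Trial objectives says the way PCT works will be explored through these variables: "coping, social support, dysfunctional attitudes, affiliation, daily stress and functioning, and their association to risk of relapse in depression, before, during and after treatment".

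Under Outcome measures/Instruments, the key to Table 1 reads "T0 = Baseline, T1 = 1 month, T2 = 2 months, T3 = 3 months", continuing to T6 at 15 months. TAU patients are followed at 1, 2, 3, 6, 12 and 15 months. For the other arm, "Patients in the experimental condition will be assessed every session and after 3, 6, 12, and 15 months". Table 2 gives the instruments completed after each PCT session.

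Other parameters also puts "personality traits measured by the Personality Diagnostic Questionnaire (PDQ-4") and victimisation (IVM) in one pooled list of possible moderators, mediators and change mechanisms. It does not say which role each plays.

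**The concern.** A moderator has to be fixed before treatment can act on it. If coping is first recorded after randomisation, and after different exposure in the two arms, a coping-by-arm interaction compares patients sorted partly by what the treatment did to them. It then does not show which kinds of patient benefit, which is the reason the protocol gives for looking at moderators.

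Mediation has a related need. A pre-treatment value allows change to be estimated and improves precision, and the mediator should be measured before the relapse it is supposed to explain. The objectives promise that pre-treatment value, and the schedule does not deliver it for most of the named mediators. A baseline that was never collected cannot be recovered at analysis.

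**Working it through.** The plan gives no figure on this point. The check is a reading of the schedule against the stated aims.

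**Step 1. Position of T0 relative to randomisation.** Eligible patients receive their allocation after the baseline interview (Assessment of eligibility and baseline measures). Month 1 and session 1 therefore both fall after randomisation. Table 2 is completed after each session, so session 1 is not a pre-treatment value either.

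**Step 2. The six mediators in Trial objectives against Tables 1 and 2.** T1 and T2 belong to the TAU schedule only. The two arms share T0 and T3 to T6.

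| Mediator | Instrument | T0 | First in TAU | First in PCT | Shared by both arms |
|---|---|---|---|---|---|
| Coping | UCL | no | T1 | session 1 | T3, T4, T6 |
| Social support | SSL-I | no | T1 | session 2 | T3, T4, T6 |
| Dysfunctional attitudes | DAS | no | T1 | session 1 (DAS-17) | T3, T5 |
| Affiliation | Affiliation | no | T1 | session 2 | T3 |
| Functioning | ORS | no | T1 | session 1 | T3 |
| Daily stress | EPCL, Brugha | yes | T0 | T0 | EPCL T0, T4, T5; Brugha T0, T6 |

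Five of six have no T0 value in either arm, and for all five the first shared time point is T3.

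**Step 3. The seven moderators in Analysis.** Coping is the only one with no pre-randomisation source. Gender, duration of remission, duration of last episode, age of onset and antidepressant use are characteristics of the patient at entry. Residual symptoms are covered by HAM-D and IDS-SR, both at T0. So one of seven is affected.

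**Step 4. All self-report rows of Table 1.**
- With T0: IDS-SR, IIP-C, EQ-5D, TIC-P, PMS, Brugha, EPCL, Mastery and VAMS, which is 9.
- Without T0: PDQ-4, IVM, SSL-I, UCL, AAQ, ORS, Affiliation, PANAS-X, DAS and BDI, which is 10.
- Total: 9 + 10 = 19.

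PDQ-4 appears only at T3 and IVM only at T6, alongside the outcome interview.

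**Step 5. During treatment.** PCT is weekly for eight sessions. The article does not fix when session 1 falls relative to T0. Assume that it follows soon after baseline, so that session k falls in about week k. Sessions 4 and 8 then roughly match TAU months 1 and 2.
- ORS, DAS-17, PANAS, BDI and Affiliation are all taken at sessions 4 and 8.
- UCL (sessions 1, 3, 5, 7) misses both, with the nearest sessions 4 − 3 = 1 and 8 − 7 = 1 week away.
- SSL-I and AAQ (sessions 2, 6) miss both, with the nearest sessions 4 − 2 = 2 and 8 − 6 = 2 weeks away.

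**Step 6. Ordering.** A relapse before T3 precedes the first mediator value that the two arms share. For such patients the T3 score may reflect the relapse and cannot be taken as its cause.

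**The case against.** The strongest reply is that these analyses are exploratory, that the primary Cox analysis and the economic evaluation do not use them, and that randomisation supports a comparison of mediator levels between arms at T3 without any baseline. All of that stands. A reader might infer that the moderator and mediator analyses as a whole cannot be interpreted. The documents do not support that: six of the seven moderators and daily stress have baseline information, and all five remaining mediators are measured in both arms at T3, some of them later as well.

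A reader might also infer that the arms are out of step on every instrument during treatment. Only UCL, SSL-I and AAQ miss sessions 4 and 8, and for UCL the gap is about one week under the assumption above.

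Nor is personality a named moderator in the Analysis section. PDQ-4 and IVM appear only in the pooled list, and the article does not say that PCT aims to change personality or victimisation. The problem with those two is simply their timing.

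The BDI gap matters less than it looks. Depressive severity is also measured by HAM-D and IDS-SR, both at T0, and either could serve as a baseline covariate.

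One could say that functioning has a baseline through IIP-C. But IIP-C covers social and interpersonal functioning and is taken at T0 only, so it cannot track change. Other parameters assigns functioning to ORS.

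What survives is a direct conflict: the objectives and the Analysis section need pre-treatment values that an explicit schedule does not collect. Condensation does not explain it, because other rows of the same table do carry T0 marks.

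**Conclusion.** The point holds in limited form. As scheduled, coping cannot be a baseline moderator (one of the seven listed). Five of the six named mediators lack the pre-treatment value that Trial objectives promises. BDI has no baseline of its own, and neither PDQ-4 nor IVM can be used as a pre-randomisation moderator.

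Between-arm comparisons of the mediators at T3 and later shared points are valid. They lack baseline adjustment and clear ordering before early relapses. The primary analysis and the other six listed moderators are untouched.

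The count of five assumes that functioning means ORS, as Other parameters says. The statement about sessions 4 and 8 assumes that session 1 falls soon after baseline. The size of any bias cannot be calculated from the document. The change is worth making because the analyses serve a stated objective and the missing data cannot be supplied later.

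**What to change.** Add UCL, SSL-I, DAS, Affiliation, ORS and BDI to T0, and PDQ-4 as well if it is to be a moderator. Have them completed before allocation is disclosed. That condition needs stating, because the eligibility section mentions e-mailing the baseline self-report measures only after it describes the contact that conveys the allocation.

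The cost is a longer baseline set: 9 + 6 = 15 self-report instruments, or 16 with PDQ-4, on top of two interviews. All are already used elsewhere in the trial.

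If T0 is closed:
- remove coping from the moderator list in Analysis;
- do not use PDQ-4 or IVM as moderators;
- limit between-arm mediation analysis to shared time points from T3, and say how relapses before T3 are handled;
- correct the claim of pre-treatment assessment in Trial objectives.

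Moving UCL, SSL-I and AAQ to sessions 4 and 8 would align the arms better during treatment. It would also disturb the session-by-session process data that the Discussion presents as an aim, so it is a trade-off for the trial team and not a necessary correction.

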## Discussion

High prevalence and frequent relapse and recurrence contribute to the public health significance of MDD. MDD is considered the most disabling disorder worldwide measured in years lived with disability [1]. This trial will be the first to compare short term individual PCT to TAU following A-CT in patients with major depression. Apart from the evaluation of the effectiveness and cost-effectiveness, we examine what works for whom, by measuring potential mediators and moderators after each PCT session and throughout the entire study.

Recent studies show that although long-term continuation of AD is likely to be effective in preventing relapse and recurrence, patients prefer psychological therapies above taking ADs [14, 51]. Therefore, sequential PCT following remission on A-CT may be a good alternative or addition to TAU. Considering the substantial negative effects on quality of life and the increased societal costs associated with depression there is a need for short-term and cost-effective interventions that can be provided by any psychologist. The results of this study might improve better treatment matching by examining mediators and moderators and thereby clarifying what is best for whom. In addition, mediation variables will be examined to get more insight into the essential ingredients of the preventive CT used. This trial aims to contribute to the improvement of more efficient therapeutic interventions to prevent relapse and recurrence in depression.
